## Abstract

Triple-negative breast cancer (TNBC) is an aggressive subtype with poor prognosis, especially in patients with residual disease post-neoadjuvant chemotherapy. This phase II MIRINAE trial (KCSG-BR18-21) evaluates the efficacy and safety of atezolizumab combined with capecitabine versus capecitabine monotherapy as adjuvant treatment in TNBC patients with residual invasive cancer. The primary endpoint is the 5-year invasive disease-free survival (IDFS) rate. Secondary endpoints include IDFS in PD-L1 positive patients, distant relapse-free survival (DRFS), and overall survival (OS). This study addresses the limitations of KEYNOTE-522 by providing data on post-neoadjuvant therapies, potentially establishing a new standard of care for TNBC.

**Trial registration** This trial is registered at ClinicalTrials.gov (NCT03756298).

## Introduction

Triple negative breast cancer (TNBC) is characterized by the absence of estrogen receptor (ER), progesterone receptor (PgR) and human epidermal growth factor receptor 2 (HER2), accounting for 15–20% of all breast cancers [1]. TNBC is more likely to have clinical aggressive features such as early recurrence, drug resistance, and frequent distant metastasis at the diagnosis [1].

In patients diagnosed with early stage TNBC (stage I ~ III), neoadjuvant chemotherapy is often recommended. Achieving a pathologic complete response (pCR) after neoadjuvant chemotherapy is an important prognostic indicator that reflects longer survival and is used as a surrogate endpoint in clinical trials, particularly with TNBC [2]. Conversely, the presence of residual disease after neoadjuvant treatment is strongly associated with poor prognosis and a higher risk of recurrence [3]. Therefore, active administration of neoadjuvant chemotherapy and response-based adjuvant treatment is currently considered as a treatment option in early TNBC [4, 5].

Recently, the integration of pembrolizumab, an immune checkpoint inhibitor (ICI), into neoadjuvant chemotherapy regimens has become a standard approach, significantly improving pCR rates [6]. However, despite these advances, access to ICIs as part of neoadjuvant chemotherapy remains limited for many patients due to barriers such as cost, availability, and regulatory challenges. Moreover, considering the potential risks of irreversible immune-related toxicity of ICI, it is necessary to selectively apply it to patients who would benefit clinically. Consequently, alternative strategies must be explored to improve outcomes for high risk TNBC patients, especially those with residual disease after neoadjuvant chemotherapy. In this context, adjuvant treatment strategies for those patients are critical to addressing this unmet clinical need.

Capecitabine, an oral chemotherapeutic agent, has demonstrated clinical efficacy in the adjuvant treatment of residual TNBC following standard neoadjuvant chemotherapy. The CREATE-X trial, which included patients with HER2 negative breast cancer who did not achieve pCR after neoadjuvant chemotherapy with anthracycline and/or taxane, showed that adjuvant capecitabine improved the 5-yr disease-free survival rate to 74.1% compared to 67.6% in the control group [7]. Notably, in the subgroup analysis, the benefit was more pronounced in the TNBC subtype (HR = 0.58, 95% CI, 0.39–0.87) [7]. Although the KEYNOTE-522 trial demonstrated that neoadjuvant - adjuvant pembrolizumab treatment significantly improved event-free survival (EFS) compared with neoadjuvant chemotherapy alone in patients with early stage TNBC, regardless of the presence of pCR [8]a significant limitation of this study was the use of placebo as the control arm in the adjuvant treatment phase. This approach is not able to answer the critical question of whether pembrolizumab adds any benefit over standard adjuvant treatments such as capecitabine and thus fails to provide comprehensive guidance on optimal post-neoadjuvant adjuvant therapies for patients with residual disease.

Therefore, investigating the efficacy of combining ICIs with chemotherapeutic agents such as capecitabine in the adjuvant setting represents a promising research direction. The rationale for this combination is based on the potential synergistic effects of immunotherapy and chemotherapy to eradicate micrometastatic disease and improve long-term outcomes. Combination of capecitabine with ICI has been evaluated in small phase 2 trials, but only in metastatic setting with no new safety signals [9].

Korean Cancer Study Group (KCSG) breast cancer committee proposed a randomized, phase II trial to evaluate the potential benefit of combining anti-PD-L1 antibody, atezolizumab with capecitabine as adjuvant treatment in TNBC patients with residual disease post-neoadjuvant chemotherapy (MIRINAE study, KCSG BR18-21).

## Objectives and endpoints

### Objectives

The primary objective of the MIRINAE trial is to examine the efficacy of a combination therapy of atezolizumab and capecitabine in patients with TNBC who have either ≥ 1 cm residual invasive breast cancer and/or positive lymph nodes (≥ ypN1) after neoadjuvant chemotherapy. Secondary objectives are to determine the efficacy and safety of the combination treatment in the PD-L1 positive group and all populations. In addition, an exploratory biomarker study will be conducted.

### Endpoints

The primary endpoint is 5-yr invasive disease-free survival (IDFS) rate in the ITT population. Secondary endpoints include the 5-yr IDFS rate in the PD-L1 positive group, distant relapse free survival (DRFS) and overall survival (OS) in all populations and in the PD-L1 positive group. Secondary safety endpoints are the type, grade, frequency and severity of adverse events according NCI-CTCAE version 5.0. Secondary translational endpoints include investigating the relationship between tumor infiltrating lymphocytes (TILs), tumor mutation burden (TMB) and efficacy endpoints (Table 1).

**Table 1 Tab1:** Objectives and endpoints

Objectives	Corresponding endpoints
Primary objectives	
• To evaluate the efficacy of capecitabine and atezolizumab compared with capecitabine alone in the adjuvant setting (5-yr IDFS)	• 5-yr invasive disease free survival (IDFS) rate in ITT population. IDFS defined as the time from randomization until documented occurrence of ipsilateral or regional invasive breast cancer, distant recurrence, death, contralateral invasive breast cancer, or second primary non-breast invasive cancer
Secondary objectives	
• To evaluate the efficacy of capecitabine and atezolizumab compared with capecitabine alone in the adjuvant setting (5-yr IDFS in PD-L1 positive group, DRFS and OS in all population)	• 5-yr IDFS rate in PD-L1 positive subpopulation • DRFS (distant relapse free survival) defined as the time from randomization until documented distant disease recurrence or death from any cause, whichever occurs first in all patients and in the PD-L1 positive subpopulation • OS (overall survival) defined as the time from randomization to the date of death from any cause in all patients and in the PD-L1 positive subpopulation
• To evaluate the safety and tolerability of atezolizumab and capecitabine compared with capecitabine alone	• Occurrence and severity of adverse events as define d by NCI CTCAE v 5.0
Exploratory biomarker objectives	
• To assess predictive, prognostic, and pharmacodynamic biomarkers associated with efficacy	• Relationship between tumor infiltrating lymphocytes (TILs) and efficacy endpoints • Relationship between tumor mutation burden (TMB) and specific driver gene mutations by FoundationOne assay and efficacy endpoints. • Relationship between immune signature by RNA sequencing and efficacy endpoints.

## Methods/study design

This is a phase II, multi-center, open-label, randomized study designed to evaluate the efficacy and safety of adjuvant treatment with atezolizumab and capecitabine compared with capecitabine alone in patients with TNBC who have either ≥ 1 cm residual invasive breast cancer and/or positive lymph nodes (≥ ypN1) after neoadjuvant chemotherapy.

HER2 and estrogen receptor (ER)/progesterone receptor (PgR) status in patient’s post-neoadjuvant surgical specimens will be used to define TNBC and local laboratory assessment for HER2, ER/PgR will be used. Before randomization, PD-L1 status on tumor infiltrating immune cells (IC) and tumor cells (TC) should be determined by Ventana PD-L1 (SP142) assay. Tumor tissue from very recently obtained (surgical specimens) will be used for PD-L1 testing. In addition, surgically resected tumor tissue will be collected for adjunctive studies. Patients who have consented and are eligible will be randomized in a 1:1 ratio to receive either of the following treatment arms stratified with PD-L1 expression on IC (< 1% vs. ≥ 1%) and yp stage (I vs. II-III).

### Study treatment

Patients receive atezolizumab plus capecitabine combination after randomization to arm A. The recommended dose of atezolizumab is 1,200 mg administered as an intravenous infusion every 3 weeks for 8 cycles with capecitabine. Then, atezolizumab monotherapy will be continued every 3 weeks up to a total of 18 cycles (for one year of treatment). Capecitabine is administered at a reduced dose (2,000 mg/m2/day, day 1–14, every 3 weeks for 8 cycles) to ensure safety. In the control arm (arm B), patients receive capecitabine monotherapy (2,500 mg/m2/day, day 1–14, every 3 weeks for 8 cycles). After the completion of study treatment, patients will be examined every 3 months for 2 years, every 6 months for 3 years, and then annually follow-up (Fig. 1).

**Fig. 1 Fig1:**
[figure not shown]
Study scheme

### Study population

This study will enroll patients with TNBC who had residual invasive disease (either ≥ 1 cm residual invasive breast cancer and/or positive lymph nodes (≥ ypN1)) after anthracycline and taxane based neoadjuvant chemotherapy regardless of PD-L1 expression.

#### Key inclusion criteria

Male or female ≥ 19 years of age.Patients must have histologically confirmed ER-, PR- and HER2-negative (triple-negative) with residual invasive breast cancer, as defined by the 2010 and 2013 American Society of Clinical Oncology (ASCO) College of American Pathologists (CAP) guidelines, after completion of neoadjuvant chemotherapy; residual disease must be ≥ 1 cm in greatest dimension, and/or have macroscopically positive lymph nodes (ypN+) observed on pathologic exam.Patients must not have metastatic diseasePatients must have had neoadjuvant chemotherapy followed by surgery; the recommended neoadjuvant treatment should include 16–24 weeks of a anthracycline and taxane-based third generation chemotherapy regimen as recommended by National Comprehensive Cancer Network (NCCN) guidelines for triple negative breast cancer. Patients who cannot complete all planned treatment cycles for any reason are considered high risk and therefore are eligible for the study if they have residual disease.Patients must have completed their final breast surgery with clear resection margins for invasive cancer and ductal carcinoma in situ (DCIS) within 90 days prior to screening.Patients for whom radiation therapy (RT) to the affected breast or chest wall and regional nodal areas is clinically indicated as per NCCN treatment guidelines, should receive RT before study treatment; RT administered after registration is also allowed.Patients must have resolution of adverse events of the most recent prior chemotherapy and RT to grade 1 or less, except alopecia and ≤ grade 2 neuropathy which are allowed.Patients must not have had prior immunotherapy with anti-PD-L1, anti-PD-1, anti-CTLA4 or similar drugs.Patients must not have had prior capecitabine therapy.Patients must not have had a history of severe allergic, anaphylactic, or other hypersensitivity reactions to chimeric or humanized antibodies or fusion proteins, known hypersensitivity or allergy to biopharmaceuticals produced in Chinese hamster ovary cells or any component of the atezolizumab formulation.Patients must have ECOG performance status < 2.Patients must sign and give written informed consent for this protocol in accordance with institutional guidelines.Patients should have adequate organ function within 21 days prior to the start of study treatment (cycle 1, day1).Women of childbearing potential must have a negative urine or serum pregnancy test within 28 day prior to registration; women/men of reproductive potential must have agreed to use an effective contraceptive method for the course of the study through 150 days after the last dose of study medication.

#### Key exclusion criteria

Malignancies other than TNBC within 5 years prior to randomization, with the exception of those with well-differentiated thyroid cancer, carcinoma in situ of the cervix or basal or squamous cell skin cancer.Significant cardiovascular disease, such as New York Hear Association (NYHA) cardiac disease (class II or greater), myocardial infarction within 3 months prior to randomization, unstable arrhythmia, or unstable angina. Patients with a known left ventricular ejection fraction (LVEF) < 50% will be excluded.Patients who have a history of interstitial pneumonitis that required steroids or evidence of active pneumonitis.Known dihydropyrimidine dehydrogenase (DPD) deficiency or history of severe and unexpected reactions to fluoropyrimidine therapy in patients selected to receive capecitabine.Patients who have an active infection requiring systemic therapy.Patients who have active autoimmune disease that has required systemic treatment in past 2 years (i.e., with use of disease modifying agents, corticosteroids or immunosuppressive drugs); patients who are on a stable dose of replacement therapy (e.g., thyroxine, insulin, or physiologic corticosteroid replacement therapy for adrenal or pituitary insufficiency, etc.) are eligible for this study.Treatment with systemic immunostimulatory agents (including but not limited to interferons or IL-2) within 4 weeks or five half-lives of the drug (whichever is shorter) prior to randomization.

### Statistical considerations

#### Estimated number of enrollments

The type I error is controlled for the primary endpoint of 5-yr IDFS rate at alpha = 0.05 (two-sided). The specified sample size will allow for 80% power to detect an improvement in 5-yr IDFS rate from 65% in Arm B to 80% in Arm A. Considering 5% of drop rate, a total of 142 patients will be required in each arm. The test statistic used is the two-sided T-Test. The significance level of the test is 0.05.

#### Efficacy analysis

The ITT population will be used for the primary analysis of 5-yr IDFS rate. An estimate of the 5-yr IDFS rate and its 95% CI will be calculated for each treatment arm. The Chi-test stratified according to tumor PD-L1 status (TC or IC < 1% vs. ≥1%) and pathologic stage (yp stage I vs. II-III) will be used to test 5-yr IDFS rate which are extrapolated from Kaplan-Meier method between treatment groups at a two-sided significance level of 5%. An unstratified chi-test will also be provided.

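### The primary test is stratified by PD-L1 on tumour cells or immune cells, whereas randomisation is stratified by PD-L1 on immune cells only: a minor mismatch to reconcile

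*Protocol article*

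**What the plan says.** Methods/study design requires that "PD-L1 status on tumor infiltrating immune cells (IC) and tumor cells (TC) should be determined by Ventana PD-L1 (SP142) assay" before randomisation, so each patient has two scores at baseline. The same section allocates patients 1:1 to "treatment arms stratified with PD-L1 expression on IC", below 1% against 1% or more, and by yp stage I against II-III.

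Efficacy analysis sets the primary comparison of 5-year IDFS rates in the ITT population: "The Chi-test stratified according to tumor PD-L1 status (TC or IC", below 1% against 1% or more, and "pathologic stage (yp stage I vs. II-III". An unstratified version of the test is to be reported as well.

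Endpoints adds a subgroup: "Secondary endpoints include the 5-yr IDFS rate in the PD-L1 positive group", with DRFS and OS in the same group. Neither the Endpoints text nor Table 1 says which compartment or cut-off makes a patient PD-L1 positive.

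**The concern.** The stage factor and the 1% cut-off agree between randomisation and analysis, but the PD-L1 compartment does not. A stratified test normally conditions on the factors that constrained the allocation, because those are the groups in which balance was enforced. Here a patient with TC at or above 1% and IC below 1% is randomised in the low stratum and, on the natural reading, analysed in the high one.

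The analysis rule is also unclear on its own terms. A patient with one compartment below 1% and the other at or above it meets both halves of the rule. The high stratum could mean either compartment at or above 1%, or only both.

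Two things are at stake: whether the primary test is specified without ambiguity, and which of the two classifications defines the population for three secondary endpoints (5-year IDFS rate, DRFS, OS in PD-L1 positive patients).

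**Working it through.** **1. The plan's own sample size, and whether the mismatch touches it.** Inputs from Estimated number of enrollments: "80% power to detect an improvement in 5-yr IDFS rate from 65% in Arm B to 80% in Arm A", two-sided alpha 0.05, 5% drop-out, 142 per arm. With the unpooled normal formula:

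n = (1.960 + 0.842)² × (0.65×0.35 + 0.80×0.20) / 0.15² = 7.849 × 0.3875 / 0.0225 = 135.2 per arm.

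Allowing for drop-out, 135.2 / 0.95 = 142.3 (or 135.2 × 1.05 = 141.9), which matches 142. No stratification factor enters, so the mismatch leaves the sample size of 2 × 142 = 284 unchanged.

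**2. How each patient is classed.**

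| TC | IC | Randomisation | Analysis, high if either is ≥1% | Analysis, high only if both are ≥1% |
|---|---|---|---|---|
| <1% | <1% | low | low | low |
| ≥1% | ≥1% | high | high | high |
| ≥1% | <1% | low | **high** | low |
| <1% | ≥1% | high | high | **low** |

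Both readings disagree with randomisation, for different patients.

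**3. How many move (natural reading: either compartment).** The article gives no PD-L1 distribution, so these shares are assumptions. With 40% IC ≥1% (0.40 × 284 = 114 patients) and a share q of the other 60% having TC ≥1%, the number moved is 284 × 0.60 × q:

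- q = 5%: 8.5, about 9 patients; the high group grows by 8.5/113.6 = 7%
- q = 15%: 25.6, about 26 patients; 25.6/113.6 = 23%
- q = 30%: 51.1, about 51 patients; 51.1/113.6 = 45%

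Under the other reading, only patients with IC ≥1% and TC <1% move. With the same 40%, that is at most 114.

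**4. Effect on the primary test (natural reading).** A stratified chi-square (Cochran-Mantel-Haenszel) test was simulated with 3,000 trials per scenario and 270 evaluable patients (284 × 0.95). Randomisation was in blocks of four within IC × stage. Assumptions: 40% IC ≥1%; 70% yp stage II-III with a 5-year rate 10 points lower; IC either not prognostic or worth +15 points; TC with no effect of its own; a treatment effect of 0 or +15 points.

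| q | IC prognostic | Type I error, IC strata | Type I error, TC-or-IC strata | Power, IC strata | Power, TC-or-IC strata |
|---|---|---|---|---|---|
| 5% | no | 0.053 | 0.054 | 0.787 | 0.788 |
| 5% | yes | 0.042 | 0.042 | 0.818 | 0.812 |
| 15% | no | 0.055 | 0.054 | 0.805 | 0.804 |
| 15% | yes | 0.056 | 0.053 | 0.797 | 0.794 |
| 30% | no | 0.059 | 0.058 | 0.803 | 0.804 |
| 30% | yes | 0.055 | 0.053 | 0.817 | 0.812 |

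The largest differences are 0.6 points in power and 0.3 points in type I error. The simulation standard errors are √(0.8×0.2/3000) = 0.7 points for a power and √(0.05×0.95/3000) = 0.4 points for an error rate. Both tests were run on the same simulated trials, so the spread between rows is mostly noise common to both columns. Dropping the strata altogether cost at most 1.4 points of power (0.797 to 0.783).

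**5. Why no bias is expected on either reading.** TC and IC are both fixed before allocation. Within each IC × stage stratum, allocation is random with respect to TC. Cutting the strata differently can therefore produce only chance imbalance between arms.

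**The case against.** The strongest reply is that nothing measurable depends on this. The analysis factor is a baseline covariate, the simulated operating characteristics hardly change, and an unstratified test, which the mismatch cannot affect, is also planned. This stands, and it is why the point is minor. It does not remove the conflict, because the unstratified test is only additional to the primary one.

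A second reply is that a journal article condenses the full protocol, and that the definition of PD-L1 positive may well be in that protocol or in the analysis plan, neither of which is shown. This also stands: the missing subgroup definition alone would not be a finding. What remains is that the article describes the same stratification factor in two incompatible ways, so at least one section needs correcting or an explanation.

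A third reply is that the article does not show which section is wrong. Since both compartments are scored before randomisation, the Methods text could be the incomplete one. That is fair, and the fix does not presuppose the answer.

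**Conclusion.** The mismatch is real and visible in the text. The primary test as written does not use the randomised PD-L1 strata, and its TC-or-IC rule leaves discordant patients unplaced. Its effect on the primary test is negligible: under 1 point in power and type I error. That figure rests on the assumed PD-L1 shares, on a binary outcome standing in for the Kaplan-Meier 5-year rates, and on the natural reading of the rule. The other reading was not simulated, but the no-bias argument covers it too.

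A reader might infer three stronger things that the documents do not support:

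- **That the primary comparison is biased or invalid.** It is not, because both scores precede allocation.
- **That PD-L1 positive carries two stated definitions, leaving the sponsor free to choose after seeing results.** The article never formally defines the term. It offers two candidate classifications and ties the subgroup to neither, and the documents not shown may already fix it. The endpoints concerned are secondary, and the article's statement on error control names only the primary one: "The type I error is controlled for the primary endpoint of 5-yr IDFS rate at alpha = 0.05 (two-sided".
- **That IC at or above 1% must be the subgroup definition.** Nothing in the article settles that.

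Severity: minor, an improvement at no real cost.

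**What to change.** Reconcile Methods/study design with Efficacy analysis. State that the primary test is stratified by exactly the PD-L1 factor used at randomisation, together with yp stage. If Methods/study design is correct, that factor is IC below 1% against 1% or more, and the reference to TC comes out of the primary test. If a TC-or-IC rule was actually used to randomise, correct Methods/study design and spell out where a patient with one compartment on each side of 1% belongs.

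Tie the PD-L1 positive endpoints (5-year IDFS rate, DRFS, OS) to one of the two classifications before outcome data are examined. The randomisation stratum is the natural choice, because balance was enforced there. Keep the other classification as a labelled sensitivity analysis.

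The cost is a sentence or two. Both scores are required before randomisation, so no new data and no change in sample size are needed.

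### The primary test is worded as a complete-data test on Kaplan-Meier 5-year rates, so on that reading its 5% level depends on nearly all patients reaching 5 years of follow-up

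*Protocol article*

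**What the plan says.** The endpoint table makes IDFS a censored time-to-event variable: "IDFS defined as the time from randomization until documented occurrence" of one of the listed events. The primary endpoint is the 5-year rate, and it is the endpoint for which the article claims type I error control at two-sided 0.05.

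Two sections name a test for it:

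- Estimated number of enrollments: the trial has "80% power to detect an improvement in 5-yr IDFS rate from 65% in Arm B to 80% in Arm A". With dropout of 5% allowed for, this comes to 142 per arm. The method behind the calculation is then named: "The test statistic used is the two-sided T-Test".
- Efficacy analysis: a chi-test, stratified by PD-L1 status and yp stage, "will be used to test 5-yr IDFS rate which are extrapolated from Kaplan-Meier method between treatment groups". In support, "An unstratified chi-test will also be provided". A 95% CI is promised for each arm, with no method given.

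Neither section names a variance for the Kaplan-Meier rates. The article gives no accrual period, minimum follow-up or data cut-off. The Study treatment section schedules visits for 5 years after the end of treatment and yearly after that.

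**The concern.** A chi-test compares counts of patients whose status is known. A Kaplan-Meier rate at 5 years is not such a count when some patients are censored earlier. Its variance is Greenwood's, which exceeds p(1-p)/N because fewer patients remain at risk late on. Multiplying the rate by N and treating the product as a count restores the smaller variance, so the test rejects too often. A t-test on 5-year status has the same need for complete data.

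This matters because it is the test on which the trial's 5% claim rests. The wording leaves its actual level, and the power of a valid replacement, dependent on when the data are cut.

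**Working it through.** **1. The plan's own figure.** Inputs from the sample-size section: 65% vs 80%, two-sided 0.05, 80% power, 5% loss. Treating 5-year status as fully observed:

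n = [0.65×0.35 + 0.80×0.20] × (1.960 + 0.842)² / 0.15² = 0.3875 × 7.849 / 0.0225 = 135.2 per arm

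Allowing for loss, 135.2/0.95 = 142.3 (or 135.2×1.05 = 141.9). The stated 142 reproduces. A t-test calculation gives 136.1, and 143.3 after loss, so the t-test label does not move the sample size. The figure is a complete-data figure.

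**2. How far the binomial variance falls short.** Assumptions, because the article gives none: constant hazard λ, uniform accrual over 3 or 4 years, and exponential loss of 5% by 5 years. Let S(t) be the IDFS curve and G(t) the probability of still being uncensored at t. In large samples:

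- Kaplan-Meier: N×Var = S(5)² ∫₀⁵ λ dt / [S(t)G(t)]
- Chi-test on N×KM: N×Var = S(5)[1−S(5)]
- R is the first divided by the second, and the actual level of a nominal 5% test is 2[1 − Φ(1.96/√R)]

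Example with 72.5% in both arms, 4-year accrual and 2-year minimum follow-up: 0.3230/0.1994 gives R = 1.62. Then 1.96/√1.62 = 1.54, and the level is 12.4%.

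Power of the Greenwood test for 65% vs 80% is Φ(0.15/SE − 1.96), with SE² the sum of the two Kaplan-Meier variances at 142 per arm. With full follow-up SE = 0.0530 and power is 80.9%. In the 4-year/2-year case SE = 0.0666 and power is 61.5%.

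**3. Results beside simulation.** The simulations used 142 per arm and 8,000 to 10,000 runs, with a common 5-year rate of 72.5% or of 65 to 80%.

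| Accrual / minimum follow-up (years) | R | Level of chi-test on N×KM, formula | Same, simulated | Power of Greenwood test, formula |
|---|---|---|---|---|
| 3 or 4 / 5 | 1.03 | 5.3% | 5.3–5.4% | 80.9% |
| 3 / 4 | 1.08 | 5.9% | 5.6–5.9% | 78.9% |
| 4 / 4 | 1.06 | 5.7% | 6.1% | 79.5% |
| 3 / 3 | 1.33 | 9.0% | 9.0–9.3% | 70.0% |
| 4 / 3 | 1.21 | 7.5% | 7.8% | 74.2% |
| 4 / 2 | 1.62 | 12.4% | 12.1–13.6% | 61.5% |

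In the same simulations a Greenwood-based test had a level of 4.6 to 6.0%.

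**4. Variations.**

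- Stratified version (four assumed strata, Mantel-Haenszel on Kaplan-Meier-derived counts, 4,000 runs): 5.8%, 5.9%, 9.2% and 12.7% for 3/5, 3/4, 3/3 and 4/2. A Greenwood-weighted stratified test gave 5.4 to 5.9%.
- Front-loaded hazard (Weibull shape 0.7, 4-year accrual): 5.5%, 5.3%, 6.9% and 10.2% at 5, 4, 3 and 2 years' minimum. The inflation is smaller but remains.
- Crude counts, with censored patients taken as event-free: the level stays near 5% when censoring is equal in the arms. The rates are biased, however: in the 4/2 case 65%/80% becomes 72%/85%.

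**The case against.** The strongest reply is that the text never says counts will be formed from Kaplan-Meier rates. A Wald chi-square on the Kaplan-Meier difference with Greenwood variance is also a chi-test and is valid, and an analysis plan that is not shown may specify it. The word *extrapolated* may be loose English for estimated. The cut-offs behind the larger figures are assumptions. What the article does state points towards long follow-up: a 5-year endpoint, only 5% dropout, and visits beyond 5 years.

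Much of this stands. A reader might infer that the trial as planned has an inflated type I error. The document does not support that: the inflation needs both the contingency-table reading and a cut-off well short of 5 years for many patients, and the article states neither. A reader might also infer that the t-test makes 142 wrong, which step 1 rules out, or that the CI and the p-value use different variances, which cannot be known because no CI method is given. Crude counting does not inflate the level under equal censoring either.

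What does not stand is that the matter can be left to the analysis plan. The article chose to state the primary test, named two different ones, and worded both in complete-data terms. The visit schedule says how long patients are seen, not when the primary data are cut.

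**Conclusion.** The concern holds in conditional form. The two sections name different tests for one alpha-controlled endpoint, and neither, as worded, carries the Kaplan-Meier variance. Run on N×KM counts, the chi-test keeps about 5% only if nearly all patients are followed for 5 years. Under assumed 3- to 4-year accrual its level is about 6% at 4 years' minimum follow-up, 7 to 9% at 3 years, and 12 to 14% at 2 years (about 10% with a front-loaded hazard). The Greenwood test stays at about 5 to 6%, but its power falls from 81% to 70–75% at 3 years and 62–63% at 2 years. The stated 80% power is therefore also conditional on 5-year follow-up. This should be fixed, but it does not show that the trial is invalid or wrongly sized.

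**What to change.** In both statistical sections, name one primary test: the difference in Kaplan-Meier 5-year IDFS between arms with Greenwood variance, combined over strata as Σ wₛ(S_A,ₛ − S_B,ₛ) with variance Σ wₛ²(V_A,ₛ + V_B,ₛ), and the 95% CI from that same variance.

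- Use the strata applied at randomisation in the design section: PD-L1 on immune cells (<1% vs ≥1%) and yp stage (I vs II–III). The Efficacy analysis section currently defines PD-L1 by tumour or immune cells, which is a different factor and must be reconciled.
- State a rule for pooling sparse strata, since an arm-stratum with no events has an estimated variance of zero.
- Replace *extrapolated* with *estimated*.
- Set the primary data cut-off at 5 years after the last randomisation.
- Delete the t-test sentence, and state that about 80% power with 142 per arm is conditional on that follow-up.

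A complementary log-log scale and supportive stratified log-rank and Cox analyses are optional. The change needs wording only, with no added patients or visits, and should be fixed before outcomes are compared by arm. The cost is that there is no early primary readout.
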